### Interventions

#### Experimental intervention

In the experimental group, patients will receive supportive parenteral nutrition containing 600 kcal per day via a central line (e.g. intravascular port system) in addition to their regular enteral nutrition. The enteral nutrition will be documented in a specific “nutrition diary.” For the parenteral nutrition, multi-chamber-bags containing amino acids, glucose, and lipids have to be used. On demand, vitamins, electrolytes, and micronutrients (trace elements) can be added. The choice of product is left to the local home care service and is not bound to a specific manufacturer. If the patient is unable to achieve his daily calorie requirement by enteral nutrition, the missing calories will be added to the 600 kcal of parenteral nutrition. A dietary assistant or a member of the study team will recalculate the daily calorie requirement once weekly, in the framework of the routine clinical evaluation during the NACT. The daily calorie requirement is calculated as follows:women: 25 kcal/kg of the ideal body weight (IBW)men: 30 kcal/kg of the IBW

The daily supportive parenteral nutrition will start with the first day of preoperative chemotherapy until the day of surgery. The administration will be effectuated by qualified nurses and can take place at the patient’s home if an ambulatory home care service is organized. The beginning of the supportive nutritional therapy will be documented in the electronic case report form (eCRF). In addition, the home care service will record the administration on a separate log.

#### Control intervention

The control group will not receive any supportive parenteral nutrition during the preoperative chemotherapy. The enteral nutrition will be documented in a specific “nutrition diary,” since it cannot be ruled out that the control group patients will increase their calorie intake due to the participation in this trial. To ensure that patients in the control group are not at risk for malnutrition during the chemotherapy, the NRS 2002 screening will be repeated at study visit 4. If patients are not able to cover > 25–50% of their daily calorie requirement by enteral nutrition alone, they will be provided with additional supportive parenteral nutrition as well.

### Permitted and not permitted medication(s)/treatment(s)

No additional study-specific treatments will be performed within the trial. If indicated for medical reasons, all kinds of medication are permitted during the trial. Postoperative medication with adverse effects on the immune system (e.g. corticoids and other immunosuppressive agents) will be recorded in the eCRF.

### Risks

Except for the administration of the parenteral nutrition in the experimental group and the survey of questionnaires, no additional study-specific examinations or interventions outside of the clinical routine will be applied. No additional risks for study patients are anticipated, since parenteral nutrition represents a clinically established standard method and all products are approved for this indication in Germany (in-label). Parenteral nutrition during chemotherapy of malnourished patients is explicitly recommended by current clinical guidelines [1]. The implantation of a central venous port system is required for the application of the preoperative chemotherapy. The blood samples will be taken during clinical routine evaluation of chemotherapy toxicity. The surgical procedure will be performed according to local standards. Adverse effects of parenteral nutrition include a slightly increased risk of port system infections. Therefore, only qualified personnel will perform the administration of parenteral nutrition in the PERCOG trial. This mildly increased risk is outweighed by the potential benefit of reduced postoperative complications by supportive parenteral nutrition, which has already been demonstrated in intensive care unit (ICU) patients [18]. The individuals’ safety is ensured by regular study visits, enforcing GCP guidelines. Furthermore, according to AMG, each patient will be provided with insurance coverage for any potential harms from trial participation. The study will be planned, conducted, and analyzed according to all relevant national and international rules and regulations (AMG [15], ICH-GCP [16], Declaration of Helsinki [4]).

In addition, the following outcome measures have been defined as secondary endpoint measures: (1) rate of serious adverse events (SAEs) and adverse events (AEs) during NACT according to the Common Terminology Criteria for Adverse Events (CTCAE v4.03.); (2) rate of AEs/SAEs associated with the administration of parenteral nutrition according to CTCAE v4.03; (3) morbidity and mortality within 30 days postoperatively according to the Calvien Dindo classification (Table 1) [19]; (4) quality of life (QoL) according to the results of EORTC (European Organization for Research and Treatment of Cancer) QLQ-C30 questionnaire; (5) change of weight and body mass index (BMI); (6) length of postoperative hospital stay; and (7) length of postoperative ICU say.

### Data collection and management

The applicable local regulations of data privacy protection will be followed. Before inclusion, patients will be informed that any patient-related data and materials will be appropriately pseudonymized (pursuant to GCP regulations [16]) and that these data may be used for analysis and publication purposes. All trial data will be recorded in eCRFs. After inclusion, baseline data (demographical data, medical history, anthropometric data) will be documented accordingly. A physical exam will be performed and a routinely taken blood sample analyzed (see Fig. 2 for included parameters). The EORTC QLQ-C30 questionnaire for the assessment of QoL will be documented and “nutrition diaries” will be handed out and explained to all participants. In case of women with childbearing potential, a pregnancy test will also be performed. During NACT, three study visits will be performed where ECOG score, as well as AEs and SAEs will be assessed and documented in the eCRF. At visit 3 (pre-chemotherapy), data on the type, duration, and dosage of chemotherapy and any additional radiotherapy will be documented. In addition, parameters of the planned parenteral nutrition intervention, the planned application route (e.g. via intravenous port system) and the used product will be documented for patients in the experimental group.

Furthermore, the IBW will be calculated as follows:IBW men: 50 kg + (2.3 kg * [body height (in cm) – 152.4 cm]/2.54 cm); andIBW women: 45.5 kg + (2.3 kg * [body height (in cm) – 152.4 cm]/2,54 cm).

Subsequently the required daily calorie supply can be calculated as:IBW * 30 kcal for men; andIBW * 25 kcal for women.

At visit 4 after the first half of chemotherapy, ECOG score, AEs, and SAEs will be assessed for all patients. In addition, anthropometric data will be reassessed and nutrition diaries will be collected and the enteral calorie intake documented. In the control group, the nutritional risk will be reassessed using the NRS 2002 screening. If control group patients fail to meet 25–50% of their calorie demand by enteral nutrition alone, parenteral nutrition will be initiated according to the procedures in the experimental group.

At study visit 5, before the surgical procedure, the duration, dosage, and end-date of NACT will be documented. In addition, ECOG score, AEs/SAEs, anthropometric data, and nutrition diaries will be assessed. A physical exam will be performed and routine laboratory values checked for anomalies. Furthermore, the EORTC QLQ-C30 questionnaire will be re-assessed. Documented parameters of the surgical procedure (visit 6) include the type and duration of the surgical procedure performed, as well as any intraoperative complications. Postoperatively, the local study personnel will perform three study visits on which physical exams will be performed, routine laboratory values checked, and all postoperative complications documented. Visit 8 on the day of hospital discharge additionally includes documentation of the length of ICU stay and the pathology report of the tumor (TNM stage). On visit 9, the primary endpoint will be assessed by independent observers, according to the procedures explained earlier. All postoperative complications, their duration, and severity will be documented according to the Clavien Dindo classification and subsequently used for the calculation of the CCI. In addition, a physical exam will be performed and the EORTC QLQ-C30 questionnaire reassessed.

To promote complete follow-up, patients who will already have been discharged from the hospital by the time of the study visits will be compensated for any travel expenses necessary to ensure participant retention. If, however, the patient is unable to attend visit 9 due to postoperative treatment in a rehabilitation facility or for other medical reasons, a standardized protocol for evaluation and documentation will have to be filled out by the treating physician.

At the end of the clinical study, all study-relevant data must be archived for at least ten years. Patient identification lists and patient files will be separately retained in the respective study sites. The infrastructure and the personnel for the data management will be provided by the Data Management Center at the MSZ, a member of the German Network of Coordinating Centers for Clinical Trials (*Koordinierungszentren für Klinische Studien* [KKS]). The eCRFs are checked for completeness, plausibility, and correctness at entry. The investigator is responsible for the accuracy and verifiability of each entry. Validating programs as well as individual inspection of data through the MSZ will ensure completeness, validity, and plausibility. Each remaining question or missing response is documented through data clarification requests, to which the investigator is obliged to respond as quickly as possible.

### Access to data and dissemination of results

Only the sponsor, personnel authorized by the sponsor, and the trial statistician will have access to the final dataset. Limited access for local investigators will be regulated in the Clinical Trial Agreement. After completion of the clinical study, the coordinating principal investigator will prepare a multicenter manuscript of the study results for publication in a reputable scientific journal. Authorship eligibility will be regulated in the Clinical Trial Agreement. The publication of the principal results from any single-center experience within the trial is not allowed until the preparation and publication of the multicenter results.

### Monitoring

Monitoring will be performed by the MSZ, an institution experienced in the monitoring of multicenter, surgical RCTs, in order to guarantee high quality of the study conduct and data retrieval. Monitoring will be carried out in accordance with ICH-GCP guidelines [16]. Monitors will visit all participating centers on a regular basis, starting with an initiation visit at each site. Furthermore, close-out visits are planned for each center. A monitoring manual describing the scope of the monitoring activity in detail will be provided. The monitor is authorized to compare trial documents and original data in adherence to data protection rights. The investigator provides direct access of patient’s documents/original source data to the monitor at any time. The monitor will also have regular contact to all participating centers and the sponsor. Furthermore, as part of quality assurance according to GCP, the sponsor and the competent health authorities have the right to audit/inspect the trial sites and any other institutions involved in the trial.

### Safety evaluation and reporting of adverse events

All AEs/SAEs from the moment of randomization until the last study visit have to be assessed, documented, and reported by the local clinical investigator or designated sub-investigator. Postoperative complications and surgical complications do not have to be documented as AE/SAE, but will be documented according to the Clavien Dindo Classification (visits 7–9). During preoperative chemotherapy (visits 2–5), changes of laboratory parameters that are expected because of the underlying illness and that are graded < 3 according to CTCAE v4.03 do not have to be reported as AEs.

SAEs have to be reported within 24 h and will be classified by intensity, outcome, and causality. Exceptions are: (1) hospital treatment planned before inclusion in the study; (2) planned admission to the hospital for NACT; and (3) hospital admissions because of the underlying disease as long as they are not because of an aggravation of the disease.

All SAEs will be subject to a second assessment by a designated person who will be independent from the reporting investigator and the trial sponsor. According to AMG and GCP regulations, the ethics committee and the competent federal health authority will be informed of all suspected unexpected serious adverse reactions (SUSARs) and all SAEs resulting in death or being life-threatening. Safety reports resuming all AE/SAEs have to be compiled regularly by the principal investigator to reassess the risk–benefit analysis.

If a female participant gets pregnant during the trial, the investigator has to report the pregnancy to the sponsor within 24 h after becoming aware of it. It is recommended to follow-up on the pregnancy and outcome.

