In conclusion, the existing evidence implies that preoperative parenteral nutrition can reduce the rate of postoperative complications after surgery for malignancies of the upper GIT. This group of patients is exposed to an increased risk of malnutrition because of the reduced food intake due to the anatomical location of the tumor, as well as nausea and loss of appetite, which are frequently caused by the NACT. Therefore, many of these patients experience clinically relevant loss of weight during NACT.

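### SAE exception (3) is not limited to scheduled admissions, so the SAE rate during NACT rests partly on an attribution by investigators who in practice know the arm

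*Protocol article*

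**What the plan says.** All references are to the protocol article.

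- **Outcome measures.** Secondary endpoint 1 is the "rate of serious adverse events (SAEs) and adverse events (AEs) during NACT". The Safety analysis section reports AE and SAE incidence by treatment group, with Chi-square or Fisher tests.
- **Safety evaluation and reporting of adverse events, general duty.** AEs and SAEs from randomisation to the last visit "have to be assessed, documented, and reported by the local clinical investigator or designated sub-investigator".
- **Same section, SAEs.** "SAEs have to be reported within 24 h and will be classified by intensity, outcome, and causality". Three exceptions follow: (1) hospital treatment planned before inclusion, (2) planned admission for NACT, and (3) "hospital admissions because of the underlying disease as long as they are not because of an aggravation of the disease".
- **Same section, second review.** "All SAEs will be subject to a second assessment by a designated person who will be independent from the reporting investigator". This person is also independent of the sponsor.
- **Same section, laboratory changes.** A waiver for the chemotherapy period covers "changes of laboratory parameters that are expected because of the underlying illness and that are graded < 3" on the CTCAE scale; no AE report is required for these.
- **Background, end of Previous trials.** Malnutrition risk is put down to "reduced food intake due to the anatomical location of the tumor". The same sentence adds nausea and appetite loss, often caused by NACT.

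**The concern.** Exceptions (1) and (2) rest on a checkable fact: the admission was planned. Exception (3) rests on a judgement: the admission is due to the disease, but not to its aggravation. In many trials this would be a minor matter. Here the tumour's effect on eating is the condition that parenteral nutrition is meant to offset, so admissions for poor intake sit close to the treatment effect. If the person judging knows the arm, similar admissions may be called exempt in one arm and reportable in the other.

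At stake is the between-arm SAE comparison in secondary endpoint 1, together with the regular safety reports used to reassess risk and benefit. The postoperative CCI is not affected.

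The laboratory waiver raises a smaller, separate question of the same kind for AEs. Whether a low-grade change counts depends partly on whether the investigator regards it as expected from the illness.

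**Working it through.** The plan gives no figure on this point, neither an SAE rate nor an admission rate, so there is nothing of its own to reproduce. The check is mainly a reading of the text, followed by arithmetic on labelled assumptions.

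**1. What exception (3) covers.** It includes disease-related admissions scheduled after inclusion for something other than NACT, which (1) and (2) miss. It also includes unplanned ones, because nothing in it requires scheduling.

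**2. How an admission for poor intake could be classified.** Three readings are open:
- due to the tumour without aggravation: exempt;
- due to aggravation of the disease: reportable;
- due to chemotherapy: not caused by the underlying disease, so reportable.

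The Background supports both a tumour cause and a chemotherapy cause. The choice falls to the local investigator.

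**3. Does that investigator know the arm?** The article does not say so outright, and the Randomization and blinding section even speaks of unblinding the local principal investigator. The procedures nevertheless point strongly to knowledge of the arm:
- The trial is observer-blinded, and the blinded observers see only the surgical records, so they do not see NACT events.
- A study team member performs the randomisation.
- At visit 3 the route and product of parenteral nutrition are recorded for experimental patients.
- At visit 4 only controls repeat the NRS screening.

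**4. Where an exempt admission goes.** The second assessor reviews SAEs. An admission not recorded as an SAE may never reach that review. The event behind it, such as dehydration or weight loss, is not a laboratory change. It stays under the general duty and still counts as an AE in endpoint 1.

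**5. The laboratory waiver.** It needs both conditions (expected from the illness, and grade below 3), covers laboratory parameters only, and removes AE reports. It cannot change the SAE rate.

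**6. Size, by assumption only.** With 75 patients per arm (Sample size section), one patient whose only SAE is exempted lowers that arm's rate by 1/75 = 1.3 points; three lower it by 3/75 = 4.0 points.

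Recorded rate = true rate × (1 − exempted share). All rates and shares below are assumed.

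| True rate, control / nutrition | Exempted share, control / nutrition | Recorded rate, control / nutrition | Difference (control − nutrition) |
|---|---|---|---|
| 30% / 30% | 10% / 10% | 27% / 27% | 0 |
| 20% / 20% | 10% / 0% | 18% / 20% | −2 points |
| 40% / 40% | 30% / 10% | 28% / 36% | −8 points |
| 30% / 30% | 10% / 30% | 27% / 21% | +6 points |
| 30% / 20% | 10% / 0% | 27% / 20% | +7 instead of +10 |
| 30% / 20% | 30% / 0% | 21% / 20% | +1 instead of +10 |

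In the −2 and −8 point rows, the chance of a nominally significant result in the direction shown (two-sided 5%) is about 5% and 18%. In the last two rows, power falls from 29% to 17% and 4%. Equal exemption with equal true rates gives no spurious difference, and the sign reverses when exemption is heavier in the nutrition arm.

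**The case against.** The strongest case on the other side has several parts.

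- **Nutritional decline may already be reportable.** A patient newly admitted because the tumour prevents eating can well be said to have an aggravation, and decline caused by NACT lies outside exception (3). This stands. It shows that exemption is one available reading, not the necessary one.
- **The exceptions may waive only the 24-hour step.** They follow that sentence, while the general duty covers all events. This is possible, but the same sentence also governs classification, and (1) and (2) are events often not counted as SAEs at all. Sites could read it either way.
- **Deterioration is captured elsewhere.** Weight and BMI change is a secondary endpoint; diaries and anthropometric data are collected at visits 4 and 5; controls repeat the NRS screening. This stands as regards nutritional status, but none of it puts an admission back into the SAE rate.
- **A condensed article may leave the definition of aggravation to the full protocol.** That is fair for the definition. The point here is the scope of the exception as worded, which is not tied to scheduling.

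Some stronger conclusions are tempting. A reader might infer that SAEs are under-counted in controls and that the harm of withholding nutrition is hidden. The documents do not support this: the rule is worded alike for both arms, an arm-aware investigator could just as well label control admissions as aggravation, and the event remains a reportable AE. A reader might also infer that exception (3) adds only unplanned admissions, or that grade 1–2 laboratory changes drop out of the SAE comparison. Steps 1 and 5 of the working show that neither is so.

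**Conclusion.** The point holds in a limited form. Exception (3) allows an unplanned admission during NACT to be left out of SAE reporting on an attribution made by someone who in practice knows the arm, in a trial where tumour-related poor intake is the target of treatment. Admissions judged exempt may miss both the second assessment and the SAE rate in secondary endpoint 1. The laboratory waiver also depends on attribution, but for the AE rate alone.

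Direction and size cannot be derived from the documents. The assumed scenarios run from no distortion to a spurious difference of 8 points, and in either direction. The conclusion rests on two readings: that local staff know the allocation, which is inferred from the procedures, and that sites may take the exceptions as waiving SAE status and not just rapid reporting.

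This is a cheap improvement. It concerns a secondary safety endpoint that is analysed descriptively with exploratory testing, and it leaves the primary endpoint untouched.

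**What to change.** 1. Limit exception (3) to disease-related admissions scheduled in advance, whether before or after inclusion. Every unplanned admission from randomisation to surgery is then recorded as an SAE in both arms and goes to the existing second assessor. This replaces a judgement with a checkable fact, and the reporting of unplanned admissions no longer depends on how aggravation is understood.
2. Do not delete exception (3) outright, because routine admissions scheduled after inclusion would then become SAEs.
3. For the AE comparison, tabulate laboratory abnormalities by CTCAE grade from the values recorded at the study visits, in both arms and regardless of attribution. The waiver on reporting low-grade changes as AEs can then stay without affecting that table.

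The cost is protocol wording, some additional SAE forms and one programmed table. According to the Trial status section, recruitment had not started when the article was published, so at that stage the change would have come before any event was classified.

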### Statistical methods

The statistical analysis will be conducted by a group-allocation-blinded statistician from the Institute for Medical Statistics and Epidemiology of the TUM, in line with the ICH-GCP guidelines [16]. For the statistical analysis, SAS software version 9.2 or higher will be used (SAS Institute Inc., Cary, NC, USA).

#### Sample size calculation

The sample size was calculated (nQuery Advisor software version 7.0, Statistical Solutions Ltd., Cork, Ireland) based on the primary endpoints of the study. Assuming that the nutrition intervention can reduce the CCI by 10 points (with a standard deviation of 20), 69 patients have to be recruited in each group to achieve a power of 80% with a two-sided significance level of 5% using the Wilcoxon signed-rank test. Expecting a drop-out rate of 8% (based on experience from previous similar trials) a total of 150 (75 per group) patients have to be included in the study.

